## 7 ADVERSE EXPERIENCES

### 7.1 Definitions

#### 7.1.1 Adverse Event (AE)

An adverse event is any untoward medical occurrence, including an exacerbation of pre-existing condition, in a patient or clinical trial subject administered an investigational medicinal product and which does not necessarily have a causal relationship with this treatment.

An adverse event (AE) can therefore be any unfavourable and unintended sign (including an abnormal laboratory finding), symptom, or disease temporally associated with the use of an investigational medicinal product, whether or not considered related to the investigational medicinal product.

#### **Protocol-specific clarifications to this definition:**

Therapy-related cytopenias as signs of an intended antileukemic activity are by definition no adverse events. However, complications of such cytopenias (i.e. neutropenic infection, thrombocytopenic bleeding) do constitute an AE.

In order to monitor the safety of the trial participants throughout the trial, untoward medical occurrences between signature of the informed consent form and first administration of the investigational medicinal product also have to be documented as adverse events.

A pathological finding, improved or unchanged in comparison to baseline, does not constitute an adverse event.

Symptoms of the disease under study should not be classified as AEs as long as they are within the normal day-to-day fluctuation. Worsening of the underlying disease or other pre-existing conditions will be recorded as an AE.

Abnormal laboratory values without therapeutic consequences do not have to be documented on the AE form. Instead, they will be documented on the laboratory values form in the CRF only.

#### 7.1.2 Adverse Reaction (AR)

An adverse reaction is any untoward and unintended response to an investigational medicinal product related to any dose administered.

All adverse events judged by either the reporting investigator or the sponsor as having a reasonable causal relationship to a medicinal product qualify as adverse reactions. The expression reasonable causal relationship means to convey in general that there is evidence or argument to suggest a causal relationship.

### **7.1.3 Serious Adverse Event (SAE) or Serious Adverse Reaction (SAR)**

A serious adverse event or serious adverse reaction is any untoward medical occurrence or effect that at any dose

- results in death,
- is life-threatening,
- requires hospitalization or prolongation of existing inpatients' hospitalization,
- results in persistent or significant disability or incapacity,
- is a congenital abnormality or birth defect.

Comments:

- All deaths up to and including 28 days after the last protocol treatment and death after the observational period (28 days after the last protocol treatment) which deemed to be related have to be reported immediately on an SAE form with one exemption (for exemptions from immediate reporting see 7.1.3.2). The adverse event is the underlying event which caused the death.
- Life-threatening in the definition of a serious adverse event or serious adverse reaction refers to an event in which the subject was at risk of death at the time of event; it does not refer to an event which hypothetically might have caused death if it were more severe.
- Hospitalization means overnight admission.
- Hospitalization without underlying adverse event (AE) is not an SAE. Examples are:
  - Hospitalization for protocol procedures e.g. chemotherapy
  - Elective hospitalization for a pre-existing condition (i.e. a condition other than the indication for the chemotherapy) that has not worsened
  - Hospitalisation which was already planned at the beginning of the trial. Hospitalisation must have been reported at screening visit in the source data and have been performed as planned
  - Admission to a rehabilitation centre or hospice

- Hospitalization for administrative or social reasons (e.g. due to anxiety but otherwise treatable on an outpatient basis).
- Congenital abnormality or birth defect: Fathering a child under BIBF 1120 is reportable as SAE in order to identify and follow-up on outcome of pregnancy and on any congenital abnormalities. The report should be made as soon as the investigator gets knowledge of the pregnancy. Follow-up of each pregnancy will be done using specific additional questionnaires supplied by the Safety Desk. Study participants will be informed about the necessity to follow up any pregnancy starting under study participation and are requested to consent into a follow-up of the course of any pregnancy in the patient information and informed consent.
- Medical judgment should be exercised in deciding whether an adverse event/reaction is serious in other situations. Important adverse events/ reactions that are not immediately life-threatening or do not result in death or hospitalization but may jeopardize the subject or may require intervention to prevent one of the other outcomes listed in the definition above, may also be considered serious.
- A new malignancy is a medically important condition and always considered as serious adverse event according to this protocol.

#### **7.1.3.1 Protocol-specific adverse events of special interest**

The following events, independent from their seriousness, are events of special interest and have to be reported in the same timeline and manner as an SAE:

- A hepatic injury defined by the following alterations of liver parameters for patients with normal AST / ALT and bilirubin at baseline: Elevation of AST and/or ALT above >3 fold ULN combined with an elevation of bilirubin above >2 fold ULN.
- Any hollow organ perforation occurring after the first intake of study medication.

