#### 4.2.2 Exclusion criteria

- Patients with 20-30% bone marrow blasts which are qualifying for and consenting into a therapy with hypomethylating agents
- Known central nervous system manifestation of AML
- Inadequate liver function (ALT and AST  $\geq$  2.5 x ULN) if not caused by leukemic infiltration
- Known chronically active hepatitis C infection or acute hepatitis
- Chronically impaired renal function (creatinin clearance < 30 ml/min)
- Uncontrolled hypertension with a resting pressure systolic > 160 mmHg or diastolic > 95 mmHg despite adequate treatment
- severe trauma or surgery within 4 weeks of study entry
- severe, non-healing wounds, ulcer or fracture
- Uncontrolled active infection
- Concurrent malignancies other than AML or other severe diseases which in the opinion of the investigator are likely to influence the endpoint assessment
- Hypersensitivity to cytarabine (not including drug fever or exanthema)
- Phase II only: Previous treatment of AML except hydroxyurea up to 24 hours before study medication
- Phase II only: Previous therapy with tyrosine kinase inhibitors or angiogenesis inhibitors
- Parallel participation in another clinical trial for the same indication. Eligibility of patients with investigational drug therapy outside of this trial during or within 4 weeks of study entry should be discussed with the study office prior to study entry
- Any severe concomitant condition, which makes it undesirable for the patient to participate in the study or which could jeopardize compliance with the protocol

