#### 5.4.4.1 General dose modifications of BIBF1120

If a dose reduction below 100 mg once daily is required, the patient should be discontinued from the treatment with BIBF1120. After resolution of the adverse event the dose may be re-escalated at the discretion of the investigator. As a general rule, non-hematological grade 3 toxicity should be followed by permanent dose reduction of BIBF 1120. Resolution of an adverse event is defined as disappearance or reduction of the adverse event to < grade 3 toxicity. For patients with grade 2 or greater toxicities present at baseline resolution to at least baseline levels will apply. No dose reductions / dose delays are required for non-hematological toxicities which are controlled with an effective specific treatment (i.e. Nausea / Emesis).

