#### 5.4.4.3 Dose modifications for non-hematological toxicity

The general recommendations for non-hematological toxicities are listed in table 1-2.

| Table 1-2: Non-hematological Criteria for Dose Delay and Dose Modification of BIBF 1120                                                                             |                                         |                                      |
|---------------------------------------------------------------------------------------------------------------------------------------------------------------------|-----------------------------------------|--------------------------------------|
| Grade                                                                                                                                                               | Dose Delay                              | Dose Modification                    |
| Grade 0-2                                                                                                                                                           | Treat on time                           | No Change                            |
| Grade 3                                                                                                                                                             | DELAY a until $\leq$ Grade 2 | DECREASE one dose level b |
| Grade 4                                                                                                                                                             | OFF protocol therapy                    | OFF protocol therapy                 |
| a. If no recovery after 30 days delay, treatment will be discontinued
b. If a dose reduction below 100 mg once daily is required, treatment will be discontinued |                                         |                                      |

These recommendations pertain, if the adverse event is considered to be related to BIBF 1120, but not to cytarabine.

BIBF 1120 must be interrupted in the event of AST and/or ALT elevations of CTCAE Grade 3 or 4 or AST and/or ALT elevations CTCAE grade  $\geq 2$  in conjunction with bilirubin elevation of CTCAE grade  $\geq 1$  and further treatment withheld until recovery of the abnormal laboratory parameters. After recovery, BIBF 1120 should only be reintroduced with a lower dose (decrease one dose level).

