## 7.2 Period of observation, documentation and reporting

All AEs, including SAEs, will be recorded from the time of signing the informed consent until 28 days after last protocol treatment including low-dose cytarabine. Medical judgment should be used to determine the relationship, considering all relevant factors, including pattern of reaction, temporal relationship, de-challenge or re-challenge, confounding factors such as concomitant medication, concomitant diseases and relevant history. Assessment of causal relationship must be recorded for each adverse event

All AEs, including SAEs, have to be recorded on the appropriate adverse event pages in the CRF.

Documentation and assessment by the investigator includes:

- Diagnosis or Description of AE
- Date of onset and date of end of AE
- Seriousness (yes/no)

- Severity, graded according to the National Cancer Institute Common Terminology Criteria for Adverse Events (CTCAE) v 4.0 for Cancer Clinical Trials
- Causality (reasonable possibility/no reasonable possibility)
- Action taken with investigational medicinal drug (none/dose changed/drug temporarily withdrawn/drug permanently withdrawn)
- Outcome (recovered/resolved, recovering/resolving, not recovered/not resolved, recovered/resolved with sequelae, fatal, unknown)

If possible, a diagnosis rather than a list of signs, symptoms and laboratory abnormalities should be given.

All AEs, including SAE, must be followed up until the condition resolves or stabilizes. (For definition of resolution of an adverse event please see 5.4.4.1.)

All SAEs identified by the protocol as requiring immediate reporting (for exceptions, see 7.1.3.2) and all AEs of special interest (for definition, see 7.1.3.1) must be reported on the SAE form in English and transmitted by fax to the Safety Desk within 24 hours of knowledge by the investigator. This applies regardless of severity (CTCAE v 4.0 grade) and whether or not the SAE is considered related to the use of study drug by the investigator. Personal data have to be replaced by the patient registration number before forwarding any information. SAEs requiring immediate reporting will be reported to Boehringer Ingelheim by the sponsor within the format and the timelines specified in the contract between sponsor and Boehringer Ingelheim.

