#### 9.5 Data Management

For data management, an electronic database will be generated at the ZKS Muenster. The database will be equipped with an audit trail that allows for a full follow-up of the history of each item.

Data capture of the study is paper based using pre-specified case report forms (CRF). The CRF will be completed and sent to the study office within two weeks (Phase I) and within four weeks (Phase II). At the study office, the incoming CRFs will be assessed for plausibility and forwarded to the ZKS. The ZKS will try to resolve possible implausibility by queries to the responsible investigator at the involved center. The investigator has to respond by a signed written statement to be sent to the study office.

Further data processing including data entry and biometrical analysis will be done at the Institute of Biostatistics and Clinical Research of the university hospital of Münster (IBCR) and at the ZKS. This will be done in close cooperation with the coordinating investigator.

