#### **10.1.3 Documentation and retention of records**

##### **10.1.3.1 Case Report Forms (CRFs)**

The Investigator is responsible for maintaining adequate and accurate CRFs which have been designed to record all observations and other data pertinent to the clinical investigation. CRFs should be filled out completely by the Investigator or delegate as stated in the Site Delegation List. All CRFs should be completed in a neat, legible manner to ensure accurate interpretation of the data; a black ball-point pen should be used to ensure the clarity of reproduced copies of all CRFs. Corrections should be made by lining out the entry to be corrected by a single line and dating and signing the corrected entry. CRFs should be completed and sent to the ZKS within 6 weeks.

As described in the ICH GCP Guidelines (E6), 'essential documents', including CRFs, source documents, consent forms, laboratory test results, and medication inventory records, will be archived by the Investigator according to the current rules and regulations.

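### The 24-hour hepatic-injury report in Protocol 7.1.3.1 covers only patients with normal liver values at baseline, although 4.2.2 admits patients with raised values

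*Protocol*

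**What the plan says.** Section 7.1.3.1 lists two events of special interest that follow the SAE route and timeline even when they are not serious. One is hepatic injury: AST and/or ALT above 3 x ULN together with bilirubin above 2 x ULN. The definition is written "for patients with normal AST / ALT and bilirubin at baseline". Under 7.2 such an event must be "transmitted by fax to the Safety Desk within 24 hours of knowledge by the investigator".

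Section 4.2.2 excludes patients with ALT and AST at or above 2.5 x ULN, but only "if not caused by leukemic infiltration". Bilirubin is not among the exclusion criteria.

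Three other provisions bear on the point:

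- 5.4.4.3, on dosing: "BIBF 1120 must be interrupted in the event of AST and/or ALT elevations of CTCAE Grade 3 or 4". The same rule covers grade 2 or higher combined with a bilirubin rise of grade 1 or higher.
- 5.4.4.1, on resolution of toxicity: "For patients with grade 2 or greater toxicities present at baseline resolution to at least baseline levels will apply".
- 7.1.3, on seriousness: "Medical judgment should be exercised in deciding whether an adverse event/reaction is serious in other situations".

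For ordinary CRF traffic, 9.5 allows two weeks in phase I and four weeks in phase II for forms to reach the study office. Section 10.1.3.1 says "CRFs should be completed and sent to the ZKS within 6 weeks".

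**The concern.** Section 2.2.2 names dose-dependent hepatic enzyme elevation as the dose-limiting toxicity of BIBF 1120. The purpose of the special-interest category is that the sponsor hears of a possible liver injury at once, without waiting for a judgment on seriousness. As written, the patients who enter with abnormal liver values have no such alert, although the eligibility criteria let them in knowingly.

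What is at stake is the speed of the sponsor's safety review in those patients. In phase I it is partly covered by 100% monitoring (9.3) and by DMC reports after each dose level (9.1). In phase II the DMC reports come every 3 months, and source data are verified on a sampling plan.

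**Working it through.** The protocol states no figure to reproduce here, so the check sets the sections side by side.

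**Step 1: who is covered.**

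| Liver values at baseline | Eligible under 4.2.2? | Hepatic criterion in 7.1.3.1? | Interruption rule in 5.4.4.3 |
|---|---|---|---|
| AST/ALT and bilirubin normal | Yes | Yes, 24-hour report | No baseline condition |
| AST/ALT above ULN, below 2.5 x ULN | Yes | None | No baseline condition |
| AST/ALT at or above 2.5 x ULN from leukemic infiltration | Yes | None | No baseline condition |
| Bilirubin above ULN | Yes, no limit set | None | No baseline condition |

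**Step 2: does another section supply a criterion?**

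- 5.4.4.3 governs dosing and notifies nobody.
- 5.4.4.1 uses baseline only to define resolution.
- 5.4.2 counts only grade IV reactions as DLTs, and only in phase I.
- 7.1.3 leaves seriousness to judgment and gives no liver threshold.
- 7.1.3.2 works the other way. It exempts SAEs judged to be signs of leukemia progression, including laboratory abnormalities, from immediate reporting and allows 4 weeks. In 7.2 that exception is attached to SAEs and not to events of special interest. So the special-interest route would be the more dependable one for a patient with liver infiltration, and such a patient is outside it if the baseline values are raised.

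**Step 3: an illustration.** A patient enters with ALT 2 x ULN and normal bilirubin and reaches ALT 8 x ULN with bilirubin 3 x ULN. Both limits are passed (8 > 3 and 3 > 2), but the definition does not apply because ALT was above normal at baseline. Unless the investigator classes the event as serious, no 24-hour report is due.

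**Step 4: reporting times.**

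- Normal baseline: 24 hours = 1 day from the investigator's knowledge (7.2).
- Raised baseline, event not classed as serious: CRF deadline of 2 x 7 = 14 days (phase I) or 4 x 7 = 28 days (phase II) to the study office (9.5), or 6 x 7 = 42 days to the ZKS (10.1.3.1).

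The CRF figures are maximum return times, and neither section says what starts the clock. They cannot be read as days from the event.

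**Step 5: how often.** The protocol gives neither the share of patients with raised baseline values nor the rate of combined rises among them, so no number follows from it. What it does give points low. The highest dose is 200 mg twice daily, where grade 3 rises are called rare (2.2.2.1) or not observed at grade 3/4 (7.3.1.1), and bilirubin rose with the enzymes in only a few cases (2.2.2).

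**The case against.** The strongest reply is that nothing here is contradictory. Eligibility and special-interest reporting serve different purposes, and the sponsor may set the scope of an extra reporting layer. In AML a raised liver value may reflect infiltration, which 4.2.2 recognises, so a plain ULN multiple is less specific in these patients. The protocol does not give this reason, but it is a fair one. It argues for a different criterion in these patients, and does not explain having none.

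A second reply is that an investigator facing such a rise, with the drug interrupted, would probably class it as serious under 7.1.3, and the 24-hour rule would then apply unless 7.1.3.2 exempts the event. This narrows the gap. It does not close it, because that clause is discretionary, and the special-interest category exists so that the alert does not depend on it.

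Three stronger readings are tempting but unsupported:

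- **That these patients are left on drug without liver protection.** Chemistry is taken at day 5 and then weekly within each cycle (6.2), the interruption rule in 5.4.4.3 ignores baseline, and restart is only at a lower dose.
- **That the sponsor's review starts a fixed 14, 28 or 42 days late.** These are deadlines from an unstated start, so it can only be said that review may start later.
- **That a material number of patients is affected.** The protocol offers no basis for such a number.

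**Conclusion.** The point holds as a minor gap in expedited notification. Eligible patients with raised AST, ALT or bilirubin at baseline have no seriousness-independent criterion for reporting hepatic injury, although liver enzyme elevation is the known dose-limiting toxicity. For a combined rise not classed as serious, the report moves from a 24-hour duty to the CRF, with return deadlines of 2, 4 or 6 weeks.

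This conclusion rests on the wording of 7.1.3.1, 4.2.2 and 7.2 and needs no assumption about frequency. The number of patients affected is unknown and likely small. Dosing protection, the response-rate endpoint, alpha and power are not touched.

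**What to change.** In 7.1.3.1, remove the restriction to normal baseline values and state:

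> AST and/or ALT >3 x ULN combined with bilirubin >2 x ULN. If the transaminase or the bilirubin was already above ULN at baseline, that value must also be higher than at baseline. A value not measured at baseline counts on its ULN multiple alone.

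The second sentence agrees with 7.1.1, under which a finding that is unchanged or better than at baseline is not an adverse event. A patient whose raised values stay where they were does not trigger a report. The third sentence is needed because 6.1.1 accepts AST or ALT alone before treatment.

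A multiple of baseline is not advisable. If doubling were required, a patient going from ALT 2 x and bilirubin 2 x ULN to ALT 10 x and bilirubin 3.9 x ULN would be missed, because 3.9 is below 2 x 2 = 4. The proposed wording captures this patient (10 > 3 and 10 > 2; 3.9 > 2). One limit remains: if a transaminase already raised at baseline does not rise further, a rise in bilirubin alone is not reported under this rule.

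The cost is a short wording change, with no new tests and no change to 4.2.2 or 5.4.4.3. There will be a few more expedited reports, some of them caused by leukemia and some by small movements above a raised baseline.

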### **2.2.2 Clinical information**

As of July 10, 2009, a total of 739 cancer patients, 423 patients with idiopathic pulmonary fibrosis and 59 healthy volunteers have been treated in multiple dose studies with BIBF 1120 or blinded BIBF 1120 / Placebo [16]. The predominant adverse events were nausea, diarrhoea, vomiting, abdominal pain and fatigue of mostly low to moderate intensity after monotherapy with BIBF 1120. Dose limiting toxicities were dose dependent hepatic enzyme elevations that were reversible after discontinuation of BIBF 1120 treatment.

These liver enzyme elevations were only in few cases accompanied by a simultaneous increase of bilirubin. In general common terminology criteria for adverse events (CTCAE, version 3.0) grade 3 liver enzyme increases were reported in the dose groups of 250 mg twice daily or higher. They also were reversible and usually occurred within the first two months of treatment.

Combination of BIBF 1120 with other anti-cancer drugs revealed a similar adverse event profile as compared to BIBF 1120 monotherapy except for the chemotherapy related toxicities. There was no change of the pharmacokinetic parameters of BIBF 1120 or of the cytotoxic compounds due to the combined treatment. Dose limiting toxicity consisted mostly of liver transaminase elevations as in the monotherapy phase I trials with the exception of the combination of BIBF 1120 with pemetrexed, where fatigue was the most relevant dose limiting toxicity.

Hypertension or thromboembolic events were rare and did not suggest an increased frequency as a consequence of therapy with BIBF 1120.

All adverse events observed in healthy volunteers after single administration of BIBF 1120 were of CTCAE Grade 1 intensity and fully reversible.

Available pharmacokinetic data indicate that the systemic exposure required for biological activity can be achieved in cancer patients. Maximum plasma concentrations occurred mainly 1 to 4 hours after administration. There was no deviation from a dose proportionality in the

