### 5.4.2 Phase I – part

The optimum dosage of BIBF 1120 in combination with low-dose cytarabine will be determined in a phase I part. Based on acceptable safety data for BIBF 1120 monotherapy, there will be a rapid dose finding. Dose finding will proceed in a classical 3+3-design. Predefined dose levels are: 100mg (dose level 1), 150mg, (dose level 2), and 200mg (dose level 3) twice daily. A cohort of three patients will be treated in each dose level and toxicity will be assessed in the first treatment cycle (28 days) by Common Terminology Criteria for Adverse Events V 4.0 (CTCAE). Patients evaluable for this safety analysis have to have received at least one dose of BIBF1120 and AraC. In case of no dose limiting toxicity (DLT), the dose will be increased by one dose level. In case of one DLT, up to three further patients will be recruited into the same dose level. If >1 DLT occurs in one dose level in up to six patients, this dose level will not be further evaluated. The highest dose level with  $\leq 1$  DLT out of six patients will be defined as the maximum tolerable dose (MTD) and will be evaluated in the phase II part of the study after approval of the data monitoring committee (DMC). Dose levels considered for phase II with less than six patients evaluated (i.e. no DLT in three patients) will further recruit patients until a total of six evaluable patients and will be chosen for phase II only if the aforementioned condition ( $\leq 1$  DLT out of six patients) applies. In case of >1 DLT in the dose level 1 cohort, the dose will be decreased to dose level 0 (100 mg BIBF 1120 once daily). The study will not proceed to the phase II part if >1 DLT occurs in dose level 0. A DLT is defined as every severe adverse reaction CTC grade IV with possible or definite relationship to the study drug BIBF1120. Therapy-related cytopenias as signs of an intended antileukemic activity do not fulfill the definition of an adverse events and therefore cannot constitute an SAE or DLT. The following known, frequent and often inevitable complications from therapy-related cytopenias are also excluded from DLT: neutropenic fever, neutropenic infections and thrombocytopenic bleedings. Notwithstanding, these complications may constitute a DLT if occurring in an unexpected high frequency, as judged by the DMC, and should be reported as an AE or SAE as appropriate (see 7). Complications attributable to disease progression in the judgement of the investigator are also excluded from DLT. These include:

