#### **7.1.3.2 Protocol-specific exceptions for immediate SAE reporting**

As mentioned above (7.1.1), hematological toxicities as signs of an effective antileukemic treatment and an intended myelosuppression do not fulfil the definition of an AE and therefore cannot constitute an SAE.

Within this study, SAEs considered as either a sometimes inevitable complication of the intended antileukemic activity or as signs of progression of the underlying disease, are

exempted from immediate reporting. SAEs considered as complication of an intended antileukemic therapy include: neutropenic fever, neutropenic infections and thrombocytopenic bleedings. Signs of leukemia progression as judged by the investigator can be:

- neutropenic infections due to disease progression\*
- thrombocytopenic bleedings due to disease progression\*
- Deterioration of the general condition due to leukemia progression\*
- Laboratory abnormalities due to leukemia progression\*
- tumor lysis syndrome due to disease progression\*
- Organ failure due to leukemia progression\*: renal insufficiency, coagulopathy, respiratory failure, hypotension
- Death due to leukemia progression\*

\*leukemia progression defined as at least one of the following: reappearance of blasts in the peripheral blood, raising blast counts in the peripheral blood, raising blast counts in bone marrow, appearance, reappearance or progression of chloromas, raising lactate dehydrogenase serum level not otherwise explained

In those cases, page one of the SAE form has to be filled out and sent to the study office Muenster together with the corresponding CRFs within 4 weeks. The study office will forward it to the Safety Desk to be entered into the SAE database.

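### Phase I dose-limiting toxicities are not on the 24-hour reporting list, so within an open dose level the 3+3 count can lag behind enrolment

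*Protocol*

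**What the plan says.** **The decision event.** Section 5.4.2: "A DLT is defined as every severe adverse reaction CTC grade IV with possible or definite relationship to the study drug BIBF1120". The window is the first 28-day cycle.

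**The rules that use it.** Same section: "In case of one DLT, up to three further patients will be recruited into the same dose level", and "If >1 DLT occurs in one dose level in up to six patients, this dose level will not be further evaluated". With no DLT in three patients, the dose goes up one level.

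**The rapid route.** Section 7.2 requires a fax to the Safety Desk within 24 hours for non-exempt SAEs and for the events of special interest in 7.1.3.1. There are two such events. One is any hollow organ perforation. The other, for patients whose AST/ALT and bilirubin were normal at baseline, is: "Elevation of AST and/or ALT above >3 fold ULN combined with an elevation of bilirubin above >2 fold ULN". DLTs are not named in either section.

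**The fallback route.** Section 9.5: "The CRF will be completed and sent to the study office within two weeks (Phase I) and within four weeks (Phase II". The text does not say when the two weeks begin.

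**The exempted SAEs.** For neutropenic fever, neutropenic infections, thrombocytopenic bleedings and signs of progression, section 7.1.3.2 asks for page one of the SAE form to be "sent to the study office Muenster together with the corresponding CRFs within 4 weeks".

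**The concern.** The decision rules and the reporting rules use different definitions. The 3+3 rules turn on severity and relatedness; the 24-hour route turns on seriousness plus two named events. The sponsor-assessment part of section 7.2 itself says that severe and serious are not the same. A DLT can therefore occur that no provision requires anyone to report quickly.

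This matters because the count is kept across several centers. If one center has the second DLT of a level and the study office does not know, another center can register and dose a patient at a level that the rule has already closed. Safety and tolerability are the primary endpoint of phase I, and the DLT is the event on which every phase I decision rests.

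**Working it through.** The plan gives no figure to reproduce here. The check compares the definitions and then counts the consequence.

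**1. One event put through each definition.** Take a grade IV AST/ALT rise, possibly related to BIBF 1120, with normal bilirubin, no admission and no actual risk of death.

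| Test | Section | Result |
|---|---|---|
| DLT | 5.4.2 | Yes: grade IV and related |
| Hepatic event of special interest | 7.1.3.1 | No: bilirubin not raised |
| SAE by a listed criterion | 7.1.3 | No: no death, actual risk of death, admission, disability or birth defect |
| SAE by judgement | 7.1.3, comments | Only if the investigator so decides; the wording permits it and does not require it |
| 24-hour report required | 7.2 | No, unless judged serious |

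Any other non-serious, related grade IV reaction gives the same result, apart from perforation and the combined hepatic event.

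**2. The lag.** On the 24-hour route it is 1 day. On the phase I CRF route it is 14 days if the clock runs from the event, which is an assumption. If it ran from the end of the cycle, an event on day 5 would be due on day 28 + 14 = 42, and the lag would be longer. I use 14 days.

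**3. Patients who can start in that time.** A level holds at most six patients, and no stagger or enrolment hold within a level is stated.
- First DLT among patients 1 to 3, second in patient 4: 6 − 4 = 2 slots are still open.
- Both DLTs among patients 1 to 3, one known and one not yet reported, with expansion opened on the known one: 6 − 3 = 3 slots are open. This requires expansion to open before the first three patients are fully assessed.

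**4. How likely it is that someone starts.** The protocol gives no phase I accrual rate. I assume 1 to 3 patients per month across centers and Poisson arrivals:

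mean = rate × lag / 30.4; P(at least one) = 1 − exp(−mean)

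| Rate per month | 14-day lag: mean, P | 1-day lag: mean, P |
|---|---|---|
| 1 | 0.46, 37% | 0.03, 3% |
| 2 | 0.92, 60% | 0.07, 6% |
| 3 | 1.38, 75% | 0.10, 9% |

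The means are before the cap set by the open slots. The probabilities are conditional: a level-closing second DLT that is not classed as serious has occurred, and a slot is open.

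**5. The two deadlines.** Section 7.1.3.2 lets page one of the SAE form and the corresponding CRFs reach the study office within four weeks. Section 9.5 wants phase I CRFs at the same office within two. Both cannot govern the same phase I forms.

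**The case against.** **The judgement clause.** Section 7.1.3 asks for medical judgement and lets an important reaction that may jeopardize the patient be called serious. A grade IV reaction attributed to BIBF 1120 is a natural candidate, and many investigators would use the clause. This stands as a limit on likelihood. It does not close the gap, because the clause is optional.

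**The transaminase example.** A reader might infer that the delay falls on the very toxicity this trial should expect. Section 2.2.2 does name hepatic enzyme elevation as the dose-limiting toxicity of earlier studies and adds: "These liver enzyme elevations were only in few cases accompanied by a simultaneous increase of bilirubin". But it places grade 3 rises at 250 mg twice daily or higher, above this trial's top level of 200 mg. Section 2.2.2.1 calls grade 3 rises rare at 200 mg and, with one exception, absent below it. Section 7.3.1.1 reports no grade 3/4 rise at 200 mg or lower. The example is therefore unlikely at the trial's doses. The gap nevertheless applies to any non-serious grade IV reaction, and this combination with cytarabine is new.

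**Escalation.** A reader might also infer that patients could move to the next level on an incomplete count, for instance because a finding on day 26 need not arrive until day 26 + 14 = 40. The protocol does not support that as stated. Escalation is conditional on no DLT after a 28-day assessment, nothing says that the next level opens on day 28 without the data, and the DMC gets a safety report after each completed level (section 9.1). Day 40 also assumes a clock start that section 9.5 does not give. Between levels there is partial cover.

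**Other safeguards.** Registration is central and all phase I patients are monitored (sections 4.3.1 and 9.3). Neither section mentions DLT notification. The DMC charter (attachment K) is not shown and could contain a rule, although the investigators' reporting duties are set out in section 7.

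**Conclusion.** The point holds as a gap in reporting. A related grade IV reaction that is not serious counts as a DLT, yet its only required route is the phase I CRF. The exposure is mainly within a level that is still enrolling or being expanded: about 2, at most 3, further patients could start before a level-closing second DLT is known. The 37% to 75% chance that at least one does so rests on the assumed accrual of 1 to 3 per month and on a two-week clock running from the event. It is conditional on such a DLT having occurred, which the protocol's own safety summary makes unlikely for transaminases.

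Two further readings go too far:
- The six-week limit in section 10.1.3.1 is for receipt of CRFs at the ZKS, so it should not be read as the delay to the study office.
- The four-week limit for exempted SAEs does not delay the running count. Neutropenic fever, neutropenic infections and thrombocytopenic bleedings are excluded from DLT individually and enter only if the DMC judges their frequency unexpectedly high. What remains is a minor conflict of deadlines.

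This is a cheap improvement that makes the protocol's own level-closing rule work as intended. It does not show that the dose-finding design is unsound.

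**What to change.** Add a third item to section 7.1.3.1 and name it in section 7.2: in phase I, cycle 1, any event meeting the DLT definition of section 5.4.2 is reported within 24 hours in the same manner as an SAE, regardless of seriousness.

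As a smaller change, reconcile the four-week limit in section 7.1.3.2 with the two-week phase I limit in section 9.5, so that reports on the exempted events are in hand before the DMC report on the level. State in section 9.5 when the two weeks begin.

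The cost is a few extra faxed forms and one aligned deadline. No dose, DLT definition or clinical rule changes.
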